#### 5.8.2. Secondary Outcomes

Secondary outcomes will be analyzed according to the type and distribution of each variable. Continuous variables (i.e., Hb decrease, bleeding index, surgery duration, time to DOAC restart, hospital length of stay) will first be assessed for normality using graphical methods (e.g., histograms). Normally distributed outcomes will be analyzed using parametric tests, specifically independent-sample t-tests. If the distribution is non-normal, non-parametric methods, such as the Mann–Whitney U test, will be applied. Ordinal or categorical variables with more than two categories, such as the number of packed red cell units transfused, will be analyzed using the Chi-square test. Binary outcomes, including thromboembolic events, postoperative complications, and a Hb decrease of more than 2 mmol/L, will be analyzed using Chi-square tests, or Fisher’s exact test in cases where expected cell counts are less than five.

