## 1. Strengths and Limitations

This study addresses an urgent and clinically relevant knowledge gap regarding the optimal surgical timing for hip fracture patients on direct oral anticoagulants, with the potential to improve national and international guidelines.It utilizes a natural experiment design across seven Dutch trauma centers, leveraging existing practice variation to approximate randomization and enable real-world comparison of early surgery within 24 h versus delayed surgery 24 h or more after last direct oral anticoagulant intake, without interfering with routine clinical care, enhancing the generalizability of the findings.While the retrospective data extraction from electronic health records at predefined intervals is a limitation, all variables are prospectively predefined and standardized across participating hospitals, and regular data quality checks with structured feedback to centers are implemented to ensure consistency, completeness, and high data quality.Due to the limited number of covariates allowed in the regression model to prevent overfitting, there remains a risk of residual confounding; however, the most clinically relevant confounders will be accounted for in the analysis.A per-protocol primary analysis may be susceptible to confounding by indication; however, a pre-planned intention-to-treat analysis will assess the robustness of findings and mitigate this bias. In addition, time-dependent confounding cannot be fully excluded. Clinical or logistical factors arising during the preoperative waiting period, such as medical optimization, complications, or operating room availability, may influence both surgical timing and outcomes independent of direct oral anticoagulant status.

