### 4.2. Secondary Objectives

-To investigate the effect on other bleeding-related outcomes in this population (i.e., preoperative blood transfusions, pre- and postoperative hemoglobin difference, the bleeding index, amount of packed red blood cells administered, reoperation due to postoperative bleeding or infection, sciatic neuropraxia due to postoperative bleeding or infection, postoperative anemia and postoperative hematoma).-To investigate the effect on thromboembolic outcomes in this population (such as acute myocardial infarction, stroke, pulmonary embolism, peripheral arterial thrombosis, and deep venous thrombosis).-To investigate the effect on postoperative complications in this population (i.e., wound fluid leakage, pressure ulcer, congestive heart failure, delirium, renal insufficiency, pneumonia, urinary tract infections, deep or superficial surgical wound infection, and in-hospital falls).-To investigate the effect on in-hospital and 30-day mortality in this population.-To investigate the effect on hospital length of stay and discharge destination in this population.

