#### 5.5.2. Secondary Outcomes

Secondary outcomes include a broad range of bleeding-related outcomes, thrombotic complications, and postoperative complications, and healthcare resource utilization. Bleeding-related outcomes include preoperative blood transfusion, the number of PRBCs administered (1, 2, 3, or ≥4 units), lowest postoperative Hb and Ht levels within 24 h postoperatively, Hb decrease (ΔHb) (defined as the difference between preoperative Hb (measured at the ED) and the lowest postoperative Hb within 24 h), the bleeding index (defined as ΔHb plus the number of PRBC transfused between the ΔHb period), the number of patients experiencing a Hb decrease of more than 2 mmol/L. Estimated intraoperative blood loss will not be recorded, as it is considered too subjective, prone to outcome reporting bias, and highly susceptible to inter-rater variability. Clinical complications such as reoperation due to postoperative bleeding or infection, sciatic neuropraxia due to postoperative bleeding or infection, postoperative hematoma, and postoperative anemia will also be recorded. Lastly, administration of tranexamic acid, fibrinogen, or platelet concentrates will also be assessed.

Thrombotic complications recorded in this study comprise myocardial infarction (confirmed by electrocardiogram), stroke (confirmed by CT), pulmonary embolism (confirmed by CT-Angiography), deep vein thrombosis (confirmed by ultrasound), and peripheral arterial thrombosis (confirmed by CT-Angiography).

Other postoperative complications as determined by the Dutch Hip Fracture Audit guidelines will be assessed and include pressure ulcers, delirium, deep or superficial surgical wound infections, wound fluid leakage, days of wound fluid leakage, congestive heart failure, and in-hospital falls (all diagnosed by the attending physician or geriatrician) [54]. Additional complications include pneumonia (confirmed by chest radiograph or positive sputum culture), urinary tract infections (confirmed by a positive urine culture), renal insufficiency (defined as a >24 mL/min/1.73 m^2^ decrease in eGFR compared to admission), in-hospital mortality (recorded in hospital records), and 30-day mortality (determined through municipality records) [54].

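### Secondary outcomes are compared only by unadjusted two-sample tests, so neither confounding nor clustering by hospital is addressed for any of them

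*Protocol article*

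**What the plan says.** Section 5.8.2 (Secondary Outcomes) fixes the method by type of variable.

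- Continuous: parametric tests if normally distributed, "specifically independent-sample t-tests"; otherwise "If the distribution is non-normal, non-parametric methods, such as the Mann–Whitney U test, will be applied".
- Ordinal or with more than two categories: outcomes "such as the number of packed red cell units transfused, will be analyzed using the Chi-square test".
- Binary: "Binary outcomes, including thromboembolic events, postoperative complications, and a Hb decrease of more than 2 mmol/L, will be analyzed using Chi-square tests", with Fisher's exact test for small expected counts.

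The section names no covariate, no centre term and no matching. It does not name mortality, but Section 5.5.2 lists "in-hospital mortality (recorded in hospital records), and 30-day mortality (determined through municipality records") among the additional complications. Mortality is binary, so the chi-square/Fisher rule covers it.

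Section 5.8.1 (Primary Outcome) holds all the safeguards. The adjusted odds ratio is for transfusion requirement, propensity matching tests the robustness of the primary findings, and a multilevel logistic model replaces the standard logistic model if clustering is detected.

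Section 4.2 words the secondary aims causally, for example "To investigate the effect on in-hospital and 30-day mortality in this population".

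**The concern.** Timing is set by hospital policy, in three hospitals against four (Section 5.2.2). A crude comparison of the two schools is therefore also a comparison of two sets of hospitals. The article accepts in Section 5.2.1 that residual confounding is possible, and in Section 1 that a per-protocol analysis is open to confounding by indication. It plans adjustment for transfusion and gives no reason why mortality or complications need less.

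One hospital makes the problem structural. It delays prosthesis surgery and performs all other procedures early (Section 5.2.2). Within that hospital, procedure type decides timing, so crude comparisons of surgical duration, Hb decrease and bleeding index are confounded by procedure there, however patients came to be admitted.

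These results will carry weight. Section 3 rests a change of practice on thrombotic as well as bleeding complications, and thrombosis is a secondary outcome only. Section 6.2 foresees further papers on it. Case-mix or hospital practice could be read as an effect of timing, with p-values that treat patients in one hospital as independent.

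**Working it through.** **The plan's own figure.** Section 5.7 gives 187 per group from event rates of 15% and 10%, a margin of 5 points, one-sided alpha 0.05 and power 90%:

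n = (1.645 + 1.282)² × (0.15×0.85 + 0.10×0.90) / (0.05 + 0.05)² = 8.567 × 0.2175 / 0.01 = 186.3, rounded up to 187.

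The figure reproduces. No stated number is in dispute; 187 per group and 374 in total are used below.

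**Scope of each safeguard.**

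| Step | Where | Outcome it is stated for |
|---|---|---|
| Multivariable logistic model | 5.8.1 | transfusion |
| Propensity score matching | 5.8.1 | primary findings |
| ICC, then multilevel logistic model | 5.8.1 | alternative to the transfusion model |
| t, Mann–Whitney, chi-square, Fisher | 5.8.2 | all secondary outcomes |

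The clustering paragraph speaks of outcomes in general, but it stands under the primary outcome and offers only a logistic model. That model could not serve length of stay, Hb decrease or bleeding index.

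**Clustering, illustrative.** The documents give no ICC, so a range is assumed. Mean hospital size is m = 374/7 = 53.4. Design effect DE = 1 + (m − 1) × ICC. Real two-sided type I error of a nominal 5% test = 2 × (1 − Φ(1.96/√DE)).

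| Assumed ICC | DE | Effective N (374/DE) | Type I error |
|---|---|---|---|
| 0 | 1.00 | 374 | 5.0% |
| 0.005 | 1.26 | 296 | 8.1% |
| 0.01 | 1.52 | 245 | 11.2% |
| 0.02 | 2.05 | 183 | 17.1% |
| 0.05 | 3.62 | 103 | 30.3% |

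Using the actual layout (187/3 = 62.3 and 187/4 = 46.75 patients per hospital) gives nearly the same: 11.4%, 17.3% and 30.7% at ICC 0.01, 0.02 and 0.05.

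**Confounding, illustrative.** Assume no true effect of timing, and outcome risk 35% in frail and 15% in other patients. Spurious difference = difference in frailty prevalence × (0.35 − 0.15).

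- 10 points (say 40% v 50% frail): 0.10 × 0.20 = 2.0 points; crude risks 23% v 25%. SE = √[(0.23×0.77 + 0.25×0.75)/187] = 0.0442, z = 0.45, two-sided rejection about 7.4%.
- 15 points (40% v 55%): 0.15 × 0.20 = 3.0 points; crude risks 23% v 26%. SE = 0.0445, z = 0.67, rejection about 10.4%.

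This stands for a fairly common outcome, with about 25% overall risk. It does not describe rare thrombotic events.

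**Cost of a full cluster correction.** With seven hospitals in two schools there are about 7 − 2 = 5 degrees of freedom, so t = 2.57 replaces 1.96. Interval width is multiplied by √DE × 2.57/1.96: 1.62 at ICC 0.01 and 1.88 at ICC 0.02, that is about 60 to 90% wider.

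**The case against.** The best defence is the design. Hospital allocation is argued to be quasi-random, the centres are described as similar in volume, staffing and perioperative care, and residual confounding is openly conceded. On that premise a crude comparison is coherent. No margin, alpha or power attaches to any secondary outcome, and detailed covariate sets are often left to an analysis plan. This limits the severity. It does not remove the point, because the crude tests are stated as the method rather than left open, and quasi-random admission does not undo the link between procedure and timing in the mixed-protocol hospital.

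Two stronger readings are tempting, and the documents do not support them.

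- A reader might infer that Section 5.8.2 contradicts the assurance in Section 1 that "the most clinically relevant confounders will be accounted for in the analysis". That clause completes a sentence about the limited number of covariates in the regression model. The only such model is the one for transfusion, so the assurance is not broken.
- A reader might infer that every secondary result will be biased. The size of any imbalance or ICC is unknown and could be small. What can be shown is that neither problem is addressed.

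Adjustment also has limits. Patient covariates cannot remove hospital-level differences such as discharge policy, and cluster methods only widen the interval around them. With few events, a model with several covariates may not be feasible.

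**Conclusion.** The point holds as a stated choice of method that should be changed: no adjustment and no allowance for clustering is planned for any secondary outcome, while the objectives are worded as effects of timing. The textual finding is firm. The sizes are not, since every ICC, prevalence and risk used is an assumption. Within those assumptions clustering is the larger concern, at two to three times the nominal error rate for ICC 0.01 to 0.02, against a false-positive rate of 7 to 10% from the frailty imbalance. At an ICC of zero with balanced groups there would be no harm. The primary non-inferiority conclusion does not depend on this point; what is said about mortality, thrombosis, complications and length of stay does.

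**What to change.** For the clinical secondary outcomes, though not for process measures such as time to surgery that differ by design:

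1. Make the main comparison a regression on school (linear, logistic or ordinal), adjusted for sex, preoperative Hb, Clinical Frailty Scale and procedure type, plus age and Charlson index where the number of events allows. Section 5.4 already collects all of these.
2. For rare outcomes, use Firth logistic regression or propensity-score weighting.
3. Report effect estimates with 95% confidence intervals. Keep the present tests as descriptive.
4. Extend the clustering assessment of Section 5.8.1 to these outcomes, with a random centre effect or small-sample cluster-robust errors. Fixed centre effects should not be used: school is almost nested in hospital, so they would absorb the contrast of interest except in the mixed-protocol hospital.
5. State that centre-level confounding cannot be removed and that the secondary results are exploratory.

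The cost is a change of wording and a little more analysis. There is no new data collection and no effect on recruitment or care. The real price is precision, as worked out above, if the full small-sample cluster correction is applied.

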### 5.7. Sample Size and Rationale for Non-Inferiority

The research question of this study is framed as a non-inferiority comparison, and the sample size has therefore been calculated to test non-inferiority. This study used the most recent institutional data, as these best reflect the clinical context and patient population of this study. These institutional data showed a transfusion rate of approximately 15% in the delayed surgery group and 10% in the early surgery group, which is considered appropriate for powering a non-inferiority analysis in this natural experiment. In consultation with clinical experts, a non-inferiority margin (ΔNI) of 5% is deemed clinically acceptable to conclude that early surgery does not result in a clinically relevant increase in transfusion requirement. Non-inferiority will be demonstrated if the upper bound of the one-sided 95% confidence interval for the absolute risk difference between groups remains below 5%. Based on these assumptions, an expected event rate of 15% in the control group and 10% in the intervention group, with a one-sided alpha of 0.05 (Zα = 1.645) and a power of 90% (Zβ = 1.282), the required total sample size is 374 patients, with 187 per group.

As the sample size is based on the per-protocol population, patient inclusion will continue until 187 patients per treatment group have been included who adhered to the protocol of their respective school of treatment (Figure 2). Inclusion in a given school will stop once the required number of per-protocol patients (*n* = 187) is reached in that group. The other school will continue including patients until it also reaches the target of 187 per-protocol patients. As a result, the intention-to-treat population is expected to exceed 374 patients. Since the primary outcome is assessed during hospitalization, no loss to follow-up is anticipated. This approach provides sufficient power to robustly assess non-inferiority within the specified parameters.

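### The number of red-cell units is treated as ordinal but tested with a chi-square that ignores the order, and no small-cell rule covers tables with more than two categories

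*Protocol article*

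**What the plan says.** Section 5.5.2 defines the outcome in ordered classes: "the number of PRBCs administered (1, 2, 3, or ≥4 units". Zero units is not among the listed classes.

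Section 5.8.2 then takes ordinal outcomes together with nominal ones of three or more levels, and gives one test for both: "such as the number of packed red cell units transfused, will be analyzed using the Chi-square test". Two other sentences of that section matter here:

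- The small-cell fallback belongs to the sentence on binary outcomes, which "will be analyzed using Chi-square tests, or Fisher’s exact test in cases where expected cell counts are less than five".
- A rank test is named only for continuous variables: "If the distribution is non-normal, non-parametric methods, such as the Mann–Whitney U test, will be applied".

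No trend test or ordinal model is mentioned. The article gives neither an expected distribution of units nor a power for this outcome.

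**The concern.** A Pearson chi-square gives the same answer if the columns are shuffled. Applied to 1, 2, 3 and ≥4 units, it spreads its sensitivity over every possible pattern instead of concentrating it on a shift towards more units, which is the pattern that would signal more bleeding. The plan recognises the variable as ordinal and already has a rank test to hand, so this is a stated choice and not a detail left to an analysis plan.

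The second problem is the missing small-cell rule. The plan considers an exact test necessary for sparse binary tables, yet states none for the larger tables, where a few dozen transfused patients are divided further.

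The study asks a safety question. A test that is less able to see a real shift makes an apparent lack of difference more likely and falsely reassuring.

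**Working it through.** **Inputs from the article (section 5.7).** The rates are "an expected event rate of 15% in the control group and 10% in the intervention group", and the sample size is calculated "with a one-sided alpha of 0.05 (Zα = 1.645) and a power of 90% (Zβ = 1.282"), with a 5% margin and 187 per group.

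**The plan's own figure.** n per group = (1.645 + 1.282)² × (0.10×0.90 + 0.15×0.85) / (0.10 − 0.15 − 0.05)² = 8.567 × 0.2175 / 0.01 = 186.3, rounded up to 187. This matches the article.

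**Expected counts.**
- Transfused patients: 187×0.10 + 187×0.15 = 18.7 + 28.05 = 46.75, about 47 (19 early, 28 delayed). The average per arm is 23.4.
- For an expected count of 5 per arm, a unit class must hold 5/23.4 = 21% of transfused patients. With the 56 events quoted in section 5.8.1 (28.05 per arm) it must hold 18%.
- An assumed mix of 50/35/10/5% over 1, 2, 3 and ≥4 units gives 11.7, 8.2, 2.3 and 1.2 per arm.
- Four other uneven mixes (40/40/12/8, 50/30/12/8, 60/25/10/5, 30/40/15/15) give 2.3 to 3.5 for 3 units and 1.2 to 3.5 for ≥4 units.
- An equal split gives 5.8 per arm. Among transfused patients alone it gives 19/4 = 4.75 in the smaller arm.

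**Power by simulation.** 40,000 tables per scenario, two-sided 5% (assumed), Pearson chi-square against the tie-corrected Mann-Whitney test.

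*Transfused patients only, the four classes of section 5.5.2, 19 v 28 patients:*

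| Mix | Arm given more units | OR | Chi-square | Mann-Whitney |
|---|---|---|---|---|
| 50/35/10/5 | delayed | 2 | 0.12 | 0.23 |
| 50/35/10/5 | delayed | 3 | 0.30–0.31 | 0.49–0.50 |
| the four other uneven mixes and the equal split | early | 2 | 0.15–0.16 | 0.24 |
| the same five mixes | early | 3 | 0.34–0.36 | 0.50–0.52 |

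The ordered test does better whichever arm is shifted. For the five mixes in the last two rows, the chi-square to Mann-Whitney power ratio is 0.63 to 0.77 over odds ratios of 2 to 4.

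*Zero units added as a fifth class, 187 per group:*

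| Scenario | Chi-square | Mann-Whitney |
|---|---|---|
| 10% v 15% transfused, same unit mix in both arms | 0.16–0.17 | 0.30–0.31 |
| 8% v 18%, mix 50/35/10/5 | 0.62 | 0.83 |
| Proportional-odds shift, OR 2 | 0.54 | 0.77 |
| OR 2.5 | 0.85 | 0.96 |
| OR 3 | 0.97 | 0.99 |
| 15% transfused in both arms, more units in one (conditional OR 3) | 0.34–0.37 | 0.05 |

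A linear trend test has power 0.25 to 0.27 in the first row and 0.13 to 0.17 in the last.

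**Size under no difference.** With zero included, the chi-square rejects in about 3.5 to 4.6% of tables at a nominal 5%. The lower value belongs to the 50/35/10/5 mix, where 99.7% of tables have at least one expected count below five.

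**The case against.** The strongest reply is that the zero-inclusive comparison says little about amount. When both arms share one unit mix, they differ only in whether patients are transfused, which is the primary outcome. A plain 2×2 test then has the same power as Mann-Whitney (0.31 at 10% v 15%), and the two agree in about 98% of simulated datasets. If instead the transfusion rates are equal and only the units per transfused patient differ, chi-square clearly beats the zero-inclusive Mann-Whitney. All of this stands. It limits which remedy is sensible, but it does not rescue the chi-square on the plan's own four classes, where the ordered test does better.

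Several stronger readings are tempting and are not supported:

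- *The chi-square halves the power.* This is true at 10% v 15% against Mann-Whitney with zero included. It is not general: the loss is about a quarter at 8% v 18%, about 3% at an odds ratio of 3, and it reverses in the case above.
- *The p-value is untrustworthy.* The error is conservative, with no excess of false positives.
- *This is the main measure of blood requirement.* The article gives no such ranking, and the bleeding index also counts transfused units.
- *Discharge destination is equally sparse.* The article gives categories but no frequencies, so this cannot be judged.

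It can also be said that sparse-table rules often sit in an analysis plan. Here, however, the article states a rule and attaches it only to binary outcomes.

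**Conclusion.** The point holds in a limited form. Section 5.8.2 gives an outcome it treats as ordinal a test that ignores the order, and it leaves tables with more than two categories without a small-cell rule. Expected counts below five in the upper classes are very probable at the planned rates, unless transfused patients are spread almost evenly over the four classes. That rests on an assumed unit distribution.

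The consequence is lost sensitivity to an ordered shift, with a slightly conservative test. On the plan's own classes the chi-square has roughly half to three quarters of the power of a rank test, for odds ratios of 2 to 4. Even the better test has low power at an odds ratio of 2, because so few patients are transfused. The outcome is secondary and unpowered, and the non-inferiority conclusion does not depend on it. This is a small improvement worth making before analysis.

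**What to change.** Change section 5.8.2 as follows:

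1. Analyse ordinal outcomes with a method that uses the order: Mann-Whitney, a trend test or a proportional-odds model.
2. For red-cell units, apply it to the classes of section 5.5.2 (1, 2, 3, ≥4) among transfused patients. Call this comparison descriptive, because it conditions on an event that occurs after surgery.
3. If a version including zero units is also reported, label it an overall shift that lies close to transfused yes or no. Do not present it as a test of amount.
4. Keep chi-square for nominal outcomes. For any table larger than 2×2 with expected counts below five, use an exact test (Fisher-Freeman-Halton or a Monte Carlo version).

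The cost is a few sentences, with no extra data or patients. The one drawback is the descriptive status of the transfused-only comparison, which should be stated openly.
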